### Recruitment {15}

Since the Department of General, Visceral and Transplant Surgery, University Medical Center of the Johannes Gutenberg-University is a certified nationwide centre of excellence in hepatobiliary surgery, patient clientele include all types of benign and malign liver resections. With a case load of about 300 liver resections per year it is deemed realistic to recruit participants within 2 years. Patients will be screened for eligibility in the outpatient clinic and if eligible offered participation on a voluntary basis.

## Assignment of interventions: allocation

### Sequence generation {16a}

After written consent and baseline assessment, patients will be randomly assigned to one of four groups at a ratio of 1:1. An envelope system utilizing opaque unmarked envelopes will be used for randomization. Randomization will be performed by an independent study nurse.

### Concealment mechanism {16b}

Randomization will be performed by an independent study nurse, who is blinded about the trial, using opaque, sealed and unmarked envelopes being drawn from a box without putting them back. Each participant will be represented in the database by a serial number.

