### Trial design {8}

The study is designed as an exploratory prospective randomized trial with even allocation into all four study groups.

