### Intervention description {11a}

After written consent, the patients are randomized into one of four groups using an envelope system. Randomization is not conducted by the researchers but by an impartial study nurse. Reconstruction of the preoperative CT scan into a 3D data set is performed by the researchers of the study group in the program Synapse 3D (Fujifilm Europe GmbH, Düsseldorf). In case of randomization into the 3D print group, the data set is anonymized and STL files are sent to a cooperating company (Cella Medical Solutions, Murcia, Spain) for printing. According to randomization, the 3D data set is then displayed to the surgeon assigned to the case not later than the day before surgery for resection planning. The surgeon is assisted by a member of the study group in terms of technical support and calculation of the planned resection volume (RLV1). At the end of surgery, the actual resection volume (RLV2) is determined by water displacement volumetry. A questionnaire about usability and subjective task load using the System Usability Scale (SUS) [19] and NASA Task Load Index (TLX) [20] is presented to the surgeons after operation. The data will be collected in a local database, to which only researchers of the study group have access. Data will be stored for 10 years according to the requirements of the local ethics committee.

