### Strategies to improve adherence to interventions {11c}

Adherence to intervention will be boosted by the technical support by the research group. Especially for surgeons, who have not used a VR head-mounted display before, help and guidance are necessary in the beginning. It is to be expected that the support needed will decrease during the course of the study.

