## Discussion

This study aims to explore the effect of different demonstration modes in planning of liver resections in order to provide surgeons with a tool to facilitate adequate planning in complex situations as well as to teach this important planning step to younger surgeons. The sample size for the study of 100 participants is expected to be attainable within two years in this high volume centre. However delayed inclusion can be seen in many clinical trials since the start of the COVID-19 pandemic, thus sufficient time to prolong recruiting, if necessary, is accounted for.

Group size of 25 patients in each group is sufficient for statistical analyses; however, it is possible that a skew between groups occurs due to very large tumours in need of extensive resection associated with higher perioperative risks. If applicable, a subgroup analysis with and without said outliers will be considered.

The trial is a first clinical test of resection planning in liver surgery in VR using a head-mounted display. Novel technologies usually raise interest at first but implementation in daily clinical use is a lengthy process, which is hardly predictable. Thus a lasting employment of VR using a head-mounted display for liver resection planning cannot be assumed. If implementation of this technology into daily practice is sustainably achieved and well accepted by users, expansion into different fields of operation planning is possible and desirable.

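### Drawing unmarked envelopes from a box leaves no predefined sequence and ties no envelope to a patient, so a redraw in this open trial could not be traced; a pre-generated list, numbered envelopes and an opening log would cure this

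*Protocol article*

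**What the plan says.** Sequence generation {16a} states that "patients will be randomly assigned to one of four groups at a ratio of 1:1" and that "An envelope system utilizing opaque unmarked envelopes will be used for randomization". Concealment mechanism {16b} adds how they are used: "opaque, sealed and unmarked envelopes being drawn from a box without putting them back". Intervention description {11a} names who draws: "Randomization is not conducted by the researchers but by an impartial study nurse". Implementation {16c} sets the order: the researchers obtain consent, report the patient's serial number to the nurse, and the nurse then randomises. The only identifier mentioned is the patient's: "Each participant will be represented in the database by a serial number".

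Three other statements bear on this. Nobody is blinded ({17a}). A surgeon who asks for another demonstration mode in a demanding case will get it ({11b}). Patients moved in this way are still to be followed and analysed with reference to their randomised group ({18b}). Trial design {8} calls the study an "exploratory prospective randomized trial with even allocation into all four study groups".

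**The concern.** The issue is verification, not foreknowledge. Loose, unmarked envelopes in a box have no first, second or third, so the allocation order comes into being only as each one is drawn. Afterwards nothing independent of the recorded arm shows that this was the arm first drawn for that patient.

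This matters more here than in a blinded trial. Everyone knows the arm once the envelope is open, and the protocol permits a later change of mode. If an envelope were opened, set aside and another drawn, the database would show the second arm as the randomised one. The analysis of patients taken out of their group, promised in {18b}, needs a randomised arm that can be shown to be the original. So does the distinction in {20a} between the per-protocol set and the patients analysed by intention to treat.

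**Working it through.** The plan gives no figure for the performance of its allocation method. Its only number here is 4 × 25 = 100 patients (Sample size {14}).

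**1. What could be reconstructed afterwards**

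- Predefined order of arms: none, because the envelopes are unmarked and drawn from a box ({16a}, {16b}).
- Link from envelope to patient: none. The serial number identifies the participant, not the envelope ({16b}, {16c}).
- Count of envelopes: possible only if the starting number is known, and it is not stated. Assume 100. After 40 patients, 60 should remain; if one had been discarded, 59 would. The count shows that one is missing, but not which patient or which draw. It shows nothing if a resealed or replacement envelope went back.
- Redraw or permitted change: {11b} allows a different mode after allocation. Without a marked envelope or a log, nothing separates that from a second draw.

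**2. Arm sizes, assuming 25 envelopes per arm**

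The box then acts as one block of 100.

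- At the end, if all are drawn: 25 in each arm, a range (largest minus smallest) of 0. Simple randomisation would give a mean range of 10.3.
- After 50 patients, the size of one arm is hypergeometric with mean 50 × 25/100 = 12.5 and SD = √[50 × 0.25 × 0.75 × (100 − 50)/(100 − 1)] = √4.73 = 2.18. The 95% range is 8 to 17.
- In simulation (10,000 to 20,000 permutations), the range after 50 patients averages 5.1 and is 6 or more in 40–41% of trials. Simple randomisation averages 7.3.
- Blocks of 4 and 8 in random order, unstratified, average 1.1 after 50 patients (95th percentile 2). Stratified by approach, they average about 1.4, with a maximum of 4.

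**3. Balance by surgical approach**

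The documents do not give the laparoscopic share, so 20%, 30% and 50% are assumed. The table shows the chance that at least one 3D arm differs from control by 20 percentage points or more in that share.

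| Scheme | 20% | 30% | 50% |
|---|---|---|---|
| Box, 25 per arm | 0.256 | 0.365 | 0.442 |
| Blocks of 4, unstratified | 0.251 | 0.364 | 0.433 |
| Blocks of 4, stratified by approach | 0 | 0 | 0 |

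Blocking alone does almost nothing for approach. Only stratification does.

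**4. Predictability**

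The guesser knows all earlier assignments and always names the arm with the fewest patients so far, with ties shared. Chance is 25%.

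| Scheme | Correct guesses |
|---|---|
| Box, 25 per arm | 33% |
| Blocks of 4 | 52% |
| Blocks of 8 | 46% |
| Blocks of 4 and 8 mixed | 49% |
| Blocks of 4 and 8 mixed, stratified (30% laparoscopic) | 48% |

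Small blocks therefore buy balance over time at a clear price in an open single-centre trial. Numbering and logging carry no such price. A list that is one random permutation of 25 per arm keeps the box's 33% and its equal final sizes.

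**The case against.** The strongest reply is that the method already does the important thing. Consent precedes the draw, the envelopes are opaque and sealed, and the person drawing is not a researcher. The next allocation is hidden from the recruiter, and the four arms finish equal if the box is filled evenly. A discarded envelope would show up in a count, and an opened one cannot easily go back. All of this stands, except that a count cannot lead back to a patient.

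The article is also a condensed account. That would answer a complaint about a missing log, but the unmarked envelopes and the box are stated as the method, and the article says that the full protocol is accessible in it ({31c}).

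A reader might infer more than the text supports:

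- *That selection bias at enrolment is likely.* The safeguards above speak against it. Composition of the coordinating centre {5d} does list one study nurse assisting in the trial, but does not say whether this is the nurse called independent in {16b}.
- *That a list would protect the measurement of planned volume.* Help from the study group in calculating it ({11a}) comes after allocation and is unaffected by how the sequence is made.
- *That the expected learning phase calls for blocking.* The sentence "It is to be expected that the support needed will decrease during the course of the study" concerns technical support, chiefly for surgeons new to the headset. No time trend across all arms is documented.
- *That the Discussion calls for stratification by approach.* It says "it is possible that a skew between groups occurs due to very large tumours"; that is not about open against laparoscopic surgery. No effect of approach on the primary quotient is documented either.

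**Conclusion.** The point holds as one of traceability. The stated mechanism has no predefined sequence and no link between envelope and patient. A repeated or discarded draw could not be traced to a patient or separated from a permitted change of mode. This follows from the wording and needs no assumption.

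Its effect on the results cannot be sized: the documents give no basis for a rate of redraws, and nothing suggests that any are expected. The finding is a modest weakness that is cheap to remove beforehand and cannot be repaired afterwards.

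Drift in arm sizes and imbalance in approach are not faults of the plan on this evidence. The drift figures assume 25 envelopes per arm; the imbalance figures also assume a laparoscopic share of 20% to 50%. Blocking, stratification and a stratified test are trade-offs the investigators may choose, not corrections they owe.

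**What to change.** Amend {16a} to {16c} before the first patient; Trial status says that recruitment had not begun.

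- The biostatistics institute named under Sample size {14} generates the allocation list by computer in advance and keeps it from the recruiters.
- Envelopes are opaque, sealed and sequentially numbered, and used strictly in order.
- The nurse writes the patient's serial number and the date on the next envelope before opening it, and enters both in an opening log.
- The log is reconciled with the list and the database. The randomised arm is recorded separately from the mode actually used.

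The cost is one list, the numbering and brief record keeping, with no extra patients. A single permutation of 25 per arm is enough for this purpose.

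Optional: if balance over time is wanted, use larger blocks of randomly varying size, withheld from recruiters. Fixed blocks of 8 still allow 46% correct guesses, so a step up from 4 to 8 gains little. If balance by surgical approach is wanted, stratify by it, since blocking alone will not provide it.

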### Implementation {16c}

The researchers of the study group will recruit participants and obtain written informed consent before inclusion into the trial. The participant is then reported to the study nurse using his or her unique serial number and the randomization is then performed by the study nurse.

## Assignment of interventions: blinding

### Who will be blinded {17a}

There is no blinding planned for this specific trial.

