### Outcomes {12}

Primary outcome is the quotient of planned resection volume (RLV1) and actual resection volume (RLV2) calculated as (RLV2-RLV1)/RLV1. The resection volume will be measured in millilitres; planned resection volume will be measured using one of the four demonstration modes and volumetry no late than the day before surgery. Actual resection volume will be measured the day of surgery. This parameter is critical to determine how accurate the predicted resection volume is between the different groups.

Secondary outcome consists of usability and subjective task load using SUS and the NASA TLX. A system is less likely to be used, if it is complicated or the controls are hard to remember or challenging to conduct. Thus these scores will show if implementation into daily clinical use is feasible for the different demonstration modes. The described systems are being tested in order to simplify liver resection planning and teaching, thus these measures are critical to determine usability and likelihood of daily use.

Furthermore, patients’ characteristics as well as intraoperative outcome (i.e. resection margin, blood loss, duration of surgery), pathological findings and postoperative morbidity and mortality are assessed in order to describe the study collective properly. Since liver resections can vary greatly in extent even in the chosen group of major resections, it is important to put patients’ characteristics and intraoperative and postoperative measures into perspective with the planned and actual surgical procedure.

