### Procedure for unblinding of needed {17b}

Not applicable since there is no blinding planned.

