## Data collection and management

### Plans for assessment and collection of outcomes {18a}

The researchers of the study group will conduct the questionnaires and be responsible for data collection. The questionnaires, scores and indices (SUS, NASA TLX, Charlson Comorbidity Index and Dindo-Clavien Scores) used in this trial have been used and validated in prior studies [17–20]. Furthermore, senior surgeons and residents will be interviewed regarding their teaching respectively learning experience. Data will be collected in a local database using SPSS Statistics Version 27 (IBM, NY, USA).

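### Nobody is blinded and no assessor is named for RLV2, so whoever measures the actual volume may already know the planned volume that it will be compared with

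*Protocol article*

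**What the plan says.** Who will be blinded {17a} reads: "There is no blinding planned for this specific trial". The next section, on unblinding {17b}, confirms it: "Not applicable since there is no blinding planned". No role is exempted.

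The endpoint is defined in Outcomes {12}: "Primary outcome is the quotient of planned resection volume (RLV1) and actual resection volume (RLV2) calculated as (RLV2-RLV1)/RLV1". The same section times the first component: "planned resection volume will be measured using one of the four demonstration modes and volumetry no late than the day before surgery". The second component follows at operation, according to Intervention description {11a}: "At the end of surgery, the actual resection volume (RLV2) is determined by water displacement volumetry". That sentence is passive and names no assessor.

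On who knows what, {11a} says that the study group builds the 3D reconstructions and that one of its members helps the surgeon calculate RLV1. Plans for assessment and collection of outcomes {18a} adds: "The researchers of the study group will conduct the questionnaires and be responsible for data collection". Section {11b} allows the 3D print and the 3D PDF into theatre for their own groups, so the arm can be visible there.

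**The concern.** The surgeon cannot be blinded to the display used for planning, but the person measuring the displaced volume can be. A manual water-displacement reading leaves some room for judgement: how far the specimen is drained, what is immersed, whether a reading is repeated. The endpoint is the distance between that reading and a number that already exists and that the assessor may know. Someone who knows the prediction may settle on a value nearer to it. If this happens more in the 3D arms, those arms look more accurate without any real gain, and accuracy of prediction is what the trial sets out to compare (Explanation for the choice of comparators {6b}). By ruling out blinding for every role, {17a} gives up a protection that is available for the one measurement on which the primary result rests.

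**Working it through.** **Is there a safeguard elsewhere in the article?**

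- Concealment mechanism {16b} describes a blinded study nurse, but she only randomises and has no stated part in measuring RLV2.
- Data management {19} provides a second-person check of database entries. That is not a second or masked reading of the volume.
- No section provides a masked, independent or duplicate reading of RLV2, or keeps RLV1 off the form on which RLV2 is written.

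So the exposure is possible under the text. The text does not show that it will occur.

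**How large could the effect be?** The article gives no figure for measurement error or drift, so there is no figure of its own to reproduce on this point. What follows is an illustration.

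Inputs from Sample size {14}: 25 patients per arm, local significance level 0.017 two-sided, SD 20% (the control-group value).

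Assumptions:

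- Both arms are truly equally accurate, so SD 20% applies to both.
- Errors are normal with mean μ.
- A fraction λ of drift occurs in one 3D arm and none in control.
- The Wilcoxon test named in {20a} is taken as the rank-sum test between two arms.

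Let q = (RLV2 − RLV1)/RLV1. If the recorded value is RLV2 − λ(RLV2 − RLV1), the recorded quotient is (1 − λ)q. Its mean is (1 − λ)μ and its SD is (1 − λ) × 20%.

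For μ = 0, the mean absolute error is SD × √(2/π) = 20% × 0.798 = 16.0%. Multiplying by 0.9, 0.8 and 0.7 gives 14.4%, 12.8% and 11.2%.

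Simulated false-positive rates per comparison, in per cent (absolute-error columns 40,000 trials with μ = 0; signed columns 10,000 trials):

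| Drift λ | SD, 3D arm | Mean absolute error (μ = 0) | Welch, absolute error | Wilcoxon, absolute error | Wilcoxon, signed, μ = 0 | Wilcoxon, signed, μ = 10% | Wilcoxon, signed, μ = 20% |
|---|---|---|---|---|---|---|---|
| 0 | 20 | 16.0 | 1.6 | 1.5 | 1.6 | 1.5 | 1.4 |
| 10% | 18 | 14.4 | 2.6 | 2.3 | 1.6 | 1.7 | 2.1 |
| 20% | 16 | 12.8 | 7.1 | 5.6 | 1.8 | 2.0 | 4.8 |
| 30% | 14 | 11.2 | 18.8 | 13.8 | 1.8 | 3.5 | 10.4 |

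The simulation standard error near the nominal level is √(0.017 × 0.983/10,000) = 0.13 percentage points, so the signed column for μ = 0 cannot be told from 1.7%. A repeat of the last cell with 20,000 trials gave 10.8%.

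The pattern follows from the formula. With μ = 0, drift leaves the centre of the signed quotient at zero and shrinks only its spread, which a rank-sum test hardly detects. With μ = 20% and λ = 0.3, the mean moves by λμ = 6 percentage points, which the test can detect. Absolute error turns the shrinkage into a difference in level whatever μ is.

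**Equal drift.** If every arm drifts by the same λ, all quotients are multiplied by the same constant. The Welch and Wilcoxon statistics are unchanged by a common scale factor, so the false-positive rate stays nominal.

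**The case against.** Four arguments carry weight.

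- Outcomes {12} defines a signed quotient and {20a} names a Wilcoxon test. A reader might infer that the 19% rate applies to the trial's primary analysis. It does not: that figure belongs to a Welch test on absolute error, and the signed analysis shows no inflation when errors centre on zero. The descriptive gain in apparent accuracy remains in either case.
- The drift fractions rest on nothing in the article, and harm requires more drift in the 3D arms than in control. An assessor who knows RLV1 could know it in the control arm too. For a hypothetical 1,000 mL plan missed by 200 mL, 30% drift means a misreading of 60 mL, which is a lot for a fairly objective method.
- A reader might also infer that the study group itself measures RLV2. The article does not say so. Being responsible for data collection is not the same as taking the reading, and {11a} leaves the assessor open.
- The surgeon helps to set RLV1, knows the arm and performs the resection, so can move RLV2 itself. A masked assessor cannot prevent that.

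The trial is also described as exploratory (Trial design {8}), which lowers the stakes.

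These arguments limit the size and certainty of the concern. They do not supply the missing safeguard. The decision against blinding is stated outright, so it cannot be put down to a condensed article.

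**Conclusion.** The point holds as a cheap improvement. The article rules out blinding for every role and leaves the RLV2 assessor unnamed. That person may therefore know RLV1, the arm or both; the text does not establish that they will.

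If drift towards RLV1 is stronger in the 3D arms, apparent accuracy there is overstated: mean absolute error falls by 1.6, 3.2 or 4.8 percentage points at 10%, 20% or 30% drift, given SD 20% and mean error 0. For the signed quotient with a Wilcoxon test, the false-positive rate stays near nominal at mean error 0 and reaches about 2%, 5% and 10–11% at mean error 20%. The higher rates of about 2.6%, 7% and 19% apply only to a Welch comparison of absolute errors. All these sizes rest on assumed drift confined to one arm. A claim that the primary test is biased as it stands would go beyond the documents.

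**What to change.** - Record RLV1 on the case report form and lock it before surgery. Put RLV2 on a separate page that shows neither RLV1 nor the allocation.
- Have RLV2 read and written down under one fixed procedure (draining, what is immersed, number of readings) by staff already present who are not told RLV1 and, where feasible, not told the arm.
- Amend {17a} to state that the RLV2 assessor is masked to RLV1 and, where feasible, to allocation, and amend {17b} to match.
- State as a remaining limitation that the unblinded surgeon can still steer the resection towards the plan.

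The cost is one extra form page and a short instruction, assuming that suitable theatre or specimen-handling staff are available; the article describes none for volumetry. Masking to arm will be imperfect when a print or PDF is in theatre, but RLV1 can still be withheld. Sample size and patient procedures do not change. Trial status says that recruitment had not begun at the time of this version, so the change could have been made before any data existed.
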